### 8.3.4 Post vaccination Observation Period (30 Minutes)

All study subjects will be observed for 30 minutes after each vaccination for any immediate reactions. If any immediate AEs (including allergic reactions) are observed during this period, the event, the time at which the event occurred within this timeframe, any concomitant medications that were administered, and resolution of the event, must be recorded on the subject's study chart as per routine clinical practice.

## 8.4 ADVERSE EVENTS (AES), ADVERSE REACTIONS (ARs) AND OTHER REPORTABLE SAFETY EVENTS

The study Investigator is responsible for detecting and documenting any event that meets the criteria and definitions of adverse event (AE) or serious adverse event (SAE) per this protocol.

During the conduct of the study, the presence of adverse events, whether serious or not, will be verified according to the definitions below.

### 8.4.1 Definitions

An **adverse event (AE)** is considered any untoward medical occurrence to the study subject, which does not necessarily have a causal relationship to the study vaccine. An AE can be any unfavorable and unintended sign (including an abnormal laboratory finding), symptom, or disease temporally associated with the study vaccine.

Any medical condition that was present before the study vaccination and that remains unchanged or improves will not be considered or recorded as an AE. A worsening of that medical condition will be considered as an AE.

A **serious adverse event (SAE)** is defined as any untoward medical occurrence that at any dose:

- results in death,
- is life-threatening,
- requires subject hospitalization or prolongation of existing hospitalization,
- results in persistent or significant disability/incapacity,
- or is a congenital anomaly/birth defect.

Life-threatening is defined as the situation in which, in the opinion of physician, the patient would have died if it had not been for a timely therapeutic intervention.

For reporting purposes, any suspected adverse events considered medically important will be classified as serious even if they do not meet the above criteria.

Medically important events are defined as those events that may not be immediately life-threatening or cause death, hospitalization, or disability, but may jeopardize the subject or require medical or surgical intervention to prevent one of the other outcomes listed above.

Examples of such events include allergic bronchospasm requiring intensive treatment at an emergency room or at home, blood dyscrasias or convulsions not requiring hospitalization, or the development of drug dependency or drug abuse.

Medical and scientific judgment should be used to decide if other situations that have resulted in one of the outcomes listed in the above definitions should be reported as a SAE.

Hospitalization or prolongation of an existing hospitalization is a criterion for considering that an AE is serious. Only admission when the patient stays overnight in the hospital should be considered hospitalization. The following situations do not meet the criteria for a SAE:

- If hospitalization or prolongation of hospitalization is required for completing a procedure required by the protocol (for instance day or night visits are performed for biopsies or surgery required by the protocol).
- If hospitalization or prolongation of hospitalization is part of the routine procedure at the site (such as withdrawal of a stent after surgery).
- If hospitalization was scheduled prior to patient entry in the study.
- If hospitalization was scheduled for a pre-existing condition that has not worsened.

An **adverse reaction (AR)** is any noxious and unintended reaction to the study vaccine, regardless of the dose administered.

An **unexpected adverse reaction (UAR)** is defined as any adverse reaction whose nature or severity is not consistent with product information (e.g., Investigator's Brochure for an unapproved investigational drug or the summary of product characteristics for an approved medicinal product).

A **suspected unexpected serious adverse reaction (SUSAR)** is an adverse reaction that is both serious and unexpected.

#### 8.4.2 Attributability Criteria

The causal relationship of the study vaccine to the occurrence of the AE/SAE will be established based on clinical judgment by the study Investigator. For this, other causes will be considered and studied, such as the natural history of underlying diseases, concomitant treatment, other risk factors, and temporal relationship of the event to the study vaccine. In addition, the summary of product characteristics of the study vaccine and concomitant therapy will be reviewed.

To analyze the possible cause-effect relationship, the temporal relationship between vaccine administration and the AE, possible alternative explanations, the outcome (complete remission, partial recovery, death, sequelae, persistence), persistence or not after discontinuation of the study vaccine, recurrence on vaccine rechallenge, or previous knowledge of the event consistent with the known or expected pattern of response to the study drug will be considered.

The causal relationship of an AE to the study vaccine will be described according to the following definitions:

**Unlikely related:** The adverse event does not occur after a plausible temporal sequence from administration of the study product and/or can be reasonably explained by other factors such as the patient's clinical state, toxic or environmental factors, or other concomitant therapies. In addition, it does not follow the known or expected pattern of response to the drug.

**Possible relationship:** The adverse event occurs after a plausible temporal sequence from administration of the study product, but can also be explained by the patient's clinical state, toxic or environmental factors, or other concomitant therapies. In addition, it does not follow the known or expected pattern of response to the drug.

**Probable relationship:** The adverse event occurs after a plausible temporal sequence from administration of the study product, cannot be reasonably explained by the patient's clinical state, toxic or environmental factors, or other concomitant therapies, and after withdrawal or dose reduction of the suspect drug, the event follows a logical clinical sequence. In addition, it follows the known or expected pattern of response to the drug.

**Clear relationship:** The adverse event occurs after a plausible temporal sequence from administration of study product cannot be reasonably explained by the patient's clinical state, toxic or environmental factors or other concomitant therapies, after withdrawal or dose reduction of the suspect drug, the event follows a logical clinical sequence, and the adverse event recurs after reintroduction of the suspect drug. In addition, it follows the known or expected pattern of response to the drug.

**No relationship:** The adverse event is clearly due to causes unrelated to the study drug, and the criteria for another causal relationship are not met.

**No assessable relationship:** Any report suggesting an adverse effect, which cannot be judged because the information is insufficient or contradictory, and which cannot be supplemented or verified.

### 8.4.3 Detection and Recording of Adverse Events

All AEs will be reported by the study subject to the Investigator at each study visit by open-ended, nonleading verbal questioning, and will be recorded based on subject's reporting, careful clinical observation of the subject and results of laboratory tests.

All AEs (serious or not) occurring during the study will be noted in the subject's medical history and recorded in the study CRF. The Investigator will also note whether the adverse event is, based on his/her judgment, related or not to the study vaccine. This decision should also be noted in the medical history and CRF.

At each visit, all AEs experienced by the patient since the previous visit should be recorded in the specific adverse event form of the CRF.

The following will be recorded for each event:

- description, severity (grade 1, 2, 3, 4 and 5),
- duration (start and end dates),
- causal relationship with the study vaccine (according to the above attributability criteria) for which this causal relationship is suspected,
- treatment (if applicable) or actions taken,
- possible alternative explanations,
- predisposing factors,
- outcome,
- for a pre-existing AE that has worsened in terms of severity or frequency, the meaning of the change should be specified.

AE's severity degree provides a qualitative assessment of the extent or intensity of an adverse event elicited by the Investigator or reported by the subject. Severity does not reflect the clinical seriousness of the event, only the grade or extent of the complaint or incidence.

The severity of an AE will be rated based on the Division of AIDS Adverse Event Grading Table.

### 8.4.4 Expedited Reporting of SAEs by the Investigator

The Investigator will report immediately to the Sponsor/representative all serious adverse events regardless of their degree of causal relationship with the study drug.

All SAEs occurring from signing of informed consent and up to 30 days after receiving the last dose of the study drug should be reported.

The initial report of SAE should be written as complete as possible, including details of the current disease and SAE and assessment of the causal relationship between the SAE and the investigational product.

Reporting will be made using the Serious Adverse Event Report Form within 24 hours from first knowledge by the Investigator, completing all information on the form in the following two days.

The information missing at the time of the initial report must be reported in the SAE follow-up form.

For SAEs, the Investigator will provide the Sponsor/representative with all documentation related to the event (additional laboratory tests, discharge reports, etc.).

The Investigator must also follow up SAEs and similarly report information related to the event until it has subsided, returned to baseline, can be attributed to products other than the study medication or to factors unrelated to conduct of the study, it is unlikely to obtain additional information, or in case of permanent impairment, until the condition stabilizes.

In the event of death, the Investigator must provide the Sponsor/representative, the Ethics Committee (EC) involved, and the relevant regulatory authorities with all additional information requested by them.

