### 1.2.2 Schedule of Activities (SoA)

|                                             | Day 1   | Month 2
(±3 weeks) | Month 6
(±4 weeks) | Month 7
(-3 weeks/
+7 weeks
from Visit 3) |
|---------------------------------------------|---------|-----------------------|-----------------------|----------------------------------------------------|
|                                             | Visit 1 | Visit 2               | Visit 3               | Visit 4                                            |
| Sign Informed Consent                       | ✓       |                       |                       |                                                    |
| Review eligibility criteria                 | ✓       |                       |                       |                                                    |
| Urine sample and pregnancy test performance | ✓       | ✓                     | ✓                     | ✓                                                  |
| Temperature (fever ≥ 37.8°C)                | ✓       | ✓                     | ✓                     | ✓                                                  |
| Questionnaire                               | ✓       | ✓                     | ✓                     | ✓                                                  |
| Height and weight measurement               | ✓       |                       |                       |                                                    |

|                                                                                                                                                |   |   |   |   |
|------------------------------------------------------------------------------------------------------------------------------------------------|---|---|---|---|
| Medical history, past and current medication and vaccination                                                                                   | ✓ | ✓ | ✓ | ✓ |
| Gynecological examination in routine visit                                                                                                     | ✓ | ✓ | ✓ | ✓ |
| Cervical sample collection                                                                                                                     | ✓ | ✓ | ✓ | ✓ |
| Vulvar sample collection                                                                                                                       | ✓ | ✓ | ✓ | ✓ |

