Study subjects will be followed thorough the whole duration of the study for possible injection-site AEs, systemic AEs, SAEs and deaths regardless of causality. All AEs and SAEs will be recorded by the study Investigator at each study visit (section 8.4).

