## 7 DISCONTINUATION OF STUDY TREATMENT AND SUBJECT WITHDRAWAL

### 7.1 DISCONTINUATION OF STUDY TREATMENT

As certain data beyond study treatment discontinuation may be important to the study, they should be collected even if the subject has decided to discontinue.

Therefore, subjects discontinuing 9vHPV vaccination prior to completion of the protocol-specified vaccination regimen will be asked to continue in the study as specified in Section 1.2 and Section 8.5.

Subjects may discontinue vaccination at any time for any reason or be discontinued at the discretion of the Investigator should any untoward effect occur. In addition, a subject may be discontinued by the Investigator or the Sponsor if study vaccination is inappropriate, the study plan is violated, or for administrative and/or other safety reasons.

A subject must be discontinued but continue to be monitored in the study for any of the following reasons:

- The subject or subject's legally acceptable representative requests to discontinue.
- The subject has a medical condition or personal circumstance which, in the opinion of the Investigator and/or Sponsor, placed the subject at unnecessary risk from continued administration of study vaccination.

If the subject becomes pregnant throughout the duration of the study, vaccination will be discontinued and resumed after childbirth. The subject may continue with other study procedures at the discretion of the Investigator.

Discontinued subjects may resume study vaccination regime if considered clinically safe and appropriate by the Investigator.

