#### 8.4.6 Expedited Reporting of SUSARs by the Sponsor

It is the responsibility of the Sponsor/ representative to communicate any SUSAR occurring from the time of subject's inclusion in the study through the complete duration of the study (7 months) to the regulatory authorities, i.e., the Spanish Agency of Medicines and Sanitary Products (AEMPS) through EudraVigilance, and to the competent bodies of the Autonomous Communities in whose territory the study is being conducted.

According to AEMPS regulations (section 8 of the AEMPS' Instructions for the Conduction of Clinical Trials), it is not necessary for the Sponsor to communicate study SUSARs to the EC.

As defined in section 8.4.1, a SUSAR is any adverse event meeting the following three criteria:

- Serious,

- Unexpected
- Associated to the administration of the study vaccine.

The study Sponsor will report the adverse experience to MSD, the study funder, as specified in the study agreement signed with MSD.

The latest deadline for SUSARs reporting will be 15 calendar days from the time the Sponsor becomes aware of the event. For SUSARs causing death or being life-threatening for the subject, the latest deadline will be 7 calendar days. When possible, complete information on the event will be provided in the following 8 days.

Information on adverse events that are not serious or unexpected and on those considered unrelated to the study vaccine will be collected in tabular form at the end of the study.

The Sponsor/representative will keep a record of all AEs reported by Investigators. These records will be submitted to the Spanish Regulatory Agency when requested.

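### The 24-hour SAE reporting window in section 8.4.4 closes 30 days after the last dose, before the safety follow-up set elsewhere ends for early stoppers and late final visits

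*Protocol*

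**What the plan says.** Four parts of the Protocol set a period for serious events.

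- **8.4.4 (investigator to sponsor):** serious events from consent onward, "up to 30 days after receiving the last dose of the study drug should be reported". The form is due within 24 hours of the investigator first knowing. The section's opening sentence asks for immediate reporting of all SAEs and gives no end date; the limit comes in the sentence after it.
- **4.1 (follow-up):** women are to be "followed thorough the whole duration of the study for possible injection-site AEs, systemic AEs, SAEs and deaths regardless of causality", with events recorded at each visit.
- **8.4.3 (CRF):** all adverse events during the study, serious or not, go into the CRF with the investigator's causality judgement, collected visit by visit. There is no 30-day limit.
- **8.4.6 (sponsor to authorities):** SUSARs from inclusion onward are to be communicated "through the complete duration of the study (7 months) to the regulatory authorities". The deadline is 15 calendar days, or 7 for fatal or life-threatening events, from the sponsor's awareness.

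Two further provisions decide whether these periods coincide. The Schedule of Activities in 1.2.2 places the final visit at "Month 7 (-3 weeks/ +7 weeks from Visit 3". Section 7.1 states that "subjects discontinuing 9vHPV vaccination prior to completion of the protocol-specified vaccination regimen will be asked to continue in the study", and 8.1.9 encourages them to attend the remaining visits.

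**The concern.** The 30-day limit is tied to the last dose, whereas the other three provisions are tied to study participation. The two end together only if dose 3 is given and Visit 4 follows about a month later. If vaccination stops early, or Visit 4 is late, the investigator's 24-hour duty ends while follow-up continues.

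The sponsor's SUSAR duty depends on that reporting route. Its clock starts at awareness, and the 24-hour form is the only route with a deadline by which an investigator makes the sponsor aware of an SAE. The women who leave this route earliest include those discontinued for an untoward effect or a medical risk. Section 7.1 requires women discontinued for medical risk to remain monitored. At stake is how soon the sponsor can judge seriousness, causality and expectedness for a late event.

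**Working it through.** No sample size or error rate is involved, so the check is calendar arithmetic.

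**Inputs**
- Doses at Day 1, Month 2 (±3 weeks) and Month 6 (±4 weeks): sections 1.2.2 and 8.1.8.1.
- Visit 4 at Month 7, window −3/+7 weeks: section 1.2.2.
- Expedited reporting to last dose + 30 days: section 8.4.4.
- Convention: 1 month = 365.25/12 = 30.44 days, Day 1 taken as day 0. Month 2 is then day 60.9 and Month 7 is day 213.1.

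**Formula:** gap = day of Visit 4 − (day of last dose + 30). A value at or below zero means no gap.

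The Visit 4 window can be read in two ways. Counted from Visit 3, it allows 3 to 7 weeks after dose 3. Counted from nominal Month 7, it allows one month −3/+7 weeks after dose 3.

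**Three doses given**
- Visit 4 on schedule: 30.4 − 30 = 0.4 days, essentially zero.
- Latest Visit 4, counted from Visit 3: 49 − 30 = 19 days.
- Latest Visit 4, counted from Month 7: 30.4 + 49 − 30 = 49.4, about 49 days.
- Earliest Visit 4: 21 − 30 = −9 days or 9.4 − 30 = −20.6 days, so no gap.

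**Vaccination stopped early, woman followed to Month 7**
- After dose 2: 213.1 − (60.9 + 30) = about 122 days.
- After dose 1: 213.1 − (0 + 30) = about 183 days.

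**Range over the visit windows for early stoppers.** This assumes that Visit 3 is still attended without vaccination. Visit 3 then falls between 182.6 − 28 = day 154.6 and 182.6 + 28 = day 210.6; dose 2 falls between day 39.9 and day 81.9.

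| Last dose | Visit 4 counted from Visit 3 | Visit 4 counted from nominal Month 7 |
|---|---|---|
| Dose 2 | 64 to 190 days | 52 to 220 days |
| Dose 1 | 146 to 230 days | 134 to 260 days |

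For example, the dose 1 lower limit counted from Visit 3 is 154.6 + 21 − 30 = 145.6, and the upper limit is 210.6 + 49 − 30 = 229.6.

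**What lapses.** The CRF duty in 8.4.3 continues, so the event is still recorded. The 24-hour step from investigator to sponsor ends. No deadline is given for CRF entry beyond the next visit, and Months 2 and 6 are nominally four months apart. An SAE that the investigator learns of between those visits could therefore wait up to that long before 8.4.3 calls for it in the CRF.

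**The case against.** The strongest reply is that the conflict is narrow. On the planned schedule, 30 days after dose 3 is Month 7, which is where the 7 months of 8.4.6 end. Recording events to the end of follow-up and expediting them for a shorter time are separate duties, so 4.1 does not by itself contradict 8.4.4. With dose 3 on time, a late Visit 4 falls after Month 7 and so outside the literal 7 months of 8.4.6. The 19-day figure fits the words in the schedule better than the 49-day one. The opening sentence of 8.4.4 has no time limit. The vaccine is licensed, and the primary endpoint, an in-vitro measure, is untouched.

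Most of this stands, and it limits the point's size. It does not remove it. For early stoppers the gap lies inside the 7 months, so 8.4.6 runs on while 8.4.4 has closed. The untimed opening sentence does not help, because a site following the protocol would apply the specific limit in the next sentence; at best the section supports two readings.

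A reader might infer more: that late SAEs go unreported, that the sponsor is bound to miss SUSAR deadlines, or that SAE counts cover different times for different women. The documents do not support these. Section 8.4.3 requires every serious event in the CRF up to the last visit, and 8.1.7 gives the sponsor access to the study database. The SUSAR clock starts at sponsor awareness, so a late report delays its start and does not breach it. Counts taken from the CRF cover each woman's whole follow-up.

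**Conclusion.** The reporting period in 8.4.4 does not match 4.1, 8.4.3 and 8.4.6, and the passages need to be reconciled. The mismatch is essentially zero for a woman with three doses seen on schedule and 19 days for the latest Visit 4 counted from Visit 3 (49 days on the other reading). To nominal Month 7 it is about 122 days after stopping at dose 2 and about 183 days after stopping at dose 1. The early-stopper figures assume that the woman does not resume vaccination, which 7.1 permits, and does not withdraw, since withdrawn women are not followed under 7.2.

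The documents give no rate of early stopping or of late final visits, so the number of women affected cannot be computed; with minimum cohorts of 39 and 30 it may be small. The consequence is possible delay in sponsor awareness and SUSAR assessment, with the events themselves still recorded. The correction is worth making because it is cheap and the text as it stands sets conflicting periods.

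**What to change.** Reconcile 4.1, 8.4.3, 8.4.4 and 8.4.6 to one SAE reporting period. In 8.4.4, let expedited reporting run from consent to the last study visit (end of participation) or 30 days after the last dose, whichever is later. This keeps the existing 30 days as a minimum and brings the gap to 0 days for every woman, whichever way the Visit 4 window is read. It also spares the investigator from deciding during follow-up whether a given dose was the last.

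The cost is one sentence in the protocol, matching instructions on the SAE form, and at most a few more SAE forms.
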